#### Items analyzed and analytical methods

The characteristics of the participants in both groups will be described statistically. Changes in the metabolic index and psychological state from enrollment to 9 months after enrollment will be compared between the two groups. The distribution of individual indices at baseline and 9 months after enrollment will be determined in the two groups, and the *t* test or a Wilcoxon rank-sum test will be performed. Analysis of covariance, multiple regression, or logistic regression will be used for factor adjustment. In addition, Fisher’s exact test will be used to compare the continuous abstinence rate in the two groups. The level of significance will be *p* ≤ 0.05. Two-tailed alpha of 5% and two-sided 95% confidence level will be used. A statistician will perform the statistical analysis.

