### Allocation and allocation adjustment factors

Potential confounding factors (age, sex, number of cigarettes smoked per day, Fagerstrom test for nicotine dependence (FTND) score, and self-rating depression scale (SDS) score) will be adjusted between the two groups via registration in the EDC system. Participants will be randomized by minimization, which is a method of dynamic allocation.

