### Intervention

#### Acquisition of data at the beginning of the study

Patient characteristics (sex, age, medical history, history of present illness, alcohol consumption, type of medications taken, and psychological state), blood chemistry measurements (white blood cell count, red blood cell count, hemoglobin, hematocrit, platelet count, fasting blood glucose, total cholesterol (T-cho), high-density lipoprotein cholesterol (HDL-cho), and triglyceride (TG)), and measurements of height, weight, blood pressure, and concentration of exhaled carbon monoxide will be examined at the beginning of the study. Smoking status (number of years of smoking, number of cigarettes smoked, tobacco dependence screener score, FTND score, age the individual started smoking, smokers in the family, and number of previous attempts to quit smoking) will be recorded during an interview at the initial visit to the smoking cessation clinic.

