#### Items observed and studied

Primary endpoint: the primary endpoint will be continuous abstinence rate. An individual is deemed to have continuously abstained from smoking if they report when interviewed that they have not smoked in the past week and if their concentration of exhaled carbon monoxide is ≤ 7 ppm [12].

Secondary endpoints: the secondary endpoints are changes in metabolic indices (height, weight, blood pressure, exhaled carbon monoxide concentration, red blood cell count, white blood cell count, hemoglobin, hematocrit, platelet count, fasting blood glucose, T-cho, HDL-cho, and TG) and changes in an individual’s psychological state (SDS score, depressive tendencies, and patient activation measure score).

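### Continuous secondary endpoints: the named comparison is an unadjusted test of change, and a baseline-adjusted ANCOVA, though mentioned, is not fixed as the main analysis

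*Protocol article*

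**What the plan says.** All of this is in the protocol article.

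- *Items observed and studied*: "the secondary endpoints are changes in metabolic indices" (weight, blood pressure, blood counts, glucose, lipids and others), together with changes in psychological state, including the SDS score.
- *Items analyzed and analytical methods*: "Changes in the metabolic index and psychological state from enrollment to 9 months after enrollment will be compared between the two groups". Next, "The distribution of individual indices at baseline and 9 months after enrollment will be determined in the two groups", and a t "test or a Wilcoxon rank-sum test will be performed". No rule for choosing between the two tests is given.
- Same section: "Analysis of covariance, multiple regression, or logistic regression will be used for factor adjustment". No endpoint is tied to any of the three models, no covariates are listed there, and nothing says whether the adjusted or the unadjusted result leads.
- *Acquisition of data at the beginning of the study*: "measurements of height, weight, blood pressure, and concentration of exhaled carbon monoxide will be examined at the beginning of the study". The same section also lists the blood tests and psychological state at baseline.
- *Allocation and allocation adjustment factors*: minimization is on age, sex, daily cigarettes, FTND score and SDS score.

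**The concern.** The baseline value of each outcome is already collected and is usually the strongest single predictor of its 9-month value. A t test or rank-sum test on the raw change uses that information inefficiently: subtracting the baseline gives it a coefficient of exactly 1, where the data would support a smaller one. Two consequences follow. The estimate is noisier than it needs to be, and a chance difference between the arms at baseline carries over into the estimated effect.

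The wording also leaves each endpoint with several possible results: t or Wilcoxon, adjusted or not. The t test compares mean changes, while the rank-sum test addresses a different hypothesis and its p-value gives no mean difference in kg or mmHg. The distributions to be examined are those of the values at the two time points, not of the change being tested, so even the implied selection rule is unclear.

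What is at stake is the precision and readability of the secondary results. Weight matters here because the abstract presents limiting weight gain as one use of the findings, although the study objective itself names only abstinence.

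**Working it through.** **The plan's own figure.** The only sample size stated is for the binary primary endpoint (*Sample size*). A control rate of 0.50 and an odds ratio of 2 give an intervention rate of 2/3. With unpooled variances, two-sided alpha 0.05 and power 0.80:

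n = (1.960 + 0.842)² × (0.250 + 0.222) / (0.1667)² = 7.85 × 0.472 / 0.0278 ≈ 133.4, so 134 per arm, as stated.

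Then 134 / 0.9 = 148.9, so 149, which the plan rounds to 150. This figure does not depend on how the secondary endpoints are analysed. Below, 134 per arm serves only as a convenient analysed size.

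**Precision.** Inputs: common variance σ² at baseline and 9 months (assumed) and baseline-to-9-month correlation ρ (not in the article; assumed, range shown).

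- Variance of change: 2σ²(1−ρ)
- Residual variance under ANCOVA: σ²(1−ρ²)
- Ratio: (1−ρ²) / [2(1−ρ)] = (1+ρ)/2
- Extra participants the change-score test needs for equal precision: 2/(1+ρ) − 1
- Power of the t test on change, for an effect that ANCOVA detects with 80% power: Φ(2.802 × √[(1+ρ)/2] − 1.960)

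| ρ (assumed) | Change, in σ² | ANCOVA, in σ² | Ratio | Extra participants | Power on change | ANCOVA n per arm matching 134 |
|---|---|---|---|---|---|---|
| 0.3 | 1.40 | 0.91 | 0.65 | 54% | 61.7% | 87 |
| 0.5 | 1.00 | 0.75 | 0.75 | 33% | 67.9% | 101 |
| 0.7 | 0.60 | 0.51 | 0.85 | 18% | 73.3% | 114 |
| 0.9 | 0.20 | 0.19 | 0.95 | 5% | 78.0% | 127 |
| 0.95 | 0.10 | 0.0975 | 0.975 | 3% | 79.0% | 131 |

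**Chance imbalance.** If the arms differ at baseline by d, the change-score difference is shifted by −(1−ρ)d. For d equal to one standard error of the baseline difference, the shift, in standard errors of the change-score difference, has size (1−ρ)/√[2(1−ρ)] = √[(1−ρ)/2]. That is 0.50, 0.39 and 0.22 for ρ = 0.5, 0.7 and 0.9. ANCOVA removes this shift.

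**Does choosing the test from the data harm the p-value?** This was simulated with 134 per arm, ρ = 0.6 and 6,000 runs per scenario. Wilcoxon replaced the t test on change when a Shapiro-Wilk test rejected normality in either arm. The effect, when present, was 0.28 baseline SD.

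| Data | Type I error, guided choice | Power, guided choice | Power, raw-scale ANCOVA |
|---|---|---|---|
| Normal | 5.3% | 72% | 81% |
| Lognormal (strongly skewed) | 4.8% | 86% | 78% |

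The simulation standard error at 5% is √(0.05 × 0.95 / 6000) = 0.28 percentage points, so neither error rate is distinguishable from 5%. The power gap with normal data agrees with the formula at ρ = 0.6 (70.7% against 80%). With strongly skewed data the order reverses, because the guided choice almost always selects Wilcoxon. Log-scale ANCOVA was not part of this simulation.

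**The case against.** **ANCOVA is already in the plan.** A reader might infer that it was passed over altogether. The text does not support that: it says that ANCOVA or a regression model will be used. What stands is narrower. It is one of three unassigned options, without a named baseline covariate, and the comparison actually described is the unadjusted one.

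**This is detail for the SAP.** Covariate lists and the rule for choosing a test are often left to an SAP, which is not shown here. That answers any complaint about missing detail. It does not fully answer this point, because the article itself names the comparison, and a better one is available from data already being collected.

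**The change-score test is valid.** This is correct. Under randomization it is unbiased, and regression to the mean acts alike on both arms in expectation. The argument is about precision and chance imbalance, not bias.

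**SDS is balanced by design.** Minimization should limit baseline imbalance in SDS, which weakens the imbalance argument for that endpoint. The other continuous outcomes are not minimization factors.

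**The choice of test does no harm.** A reader might infer that the test is picked on unblinded data and inflates the false-positive rate. Neither is supported. The trial is open-label, but the article does not say whether allocation is visible when distributions are examined. Data-driven selection is strongly implied rather than stated, and the simulation shows no inflation. What remains is that several results per endpoint are possible and none is designated as the main one.

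**ANCOVA is not always better.** On strongly skewed raw data, Wilcoxon won. This stands, and it shapes the fix.

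**Conclusion.** The point holds as a matter of efficiency and prespecification for the continuous secondary endpoints only. Under equal variances the change-score test is less precise than ANCOVA at any correlation below 1. The variance ratio is 0.75, 0.85 and 0.95 at ρ = 0.5, 0.7 and 0.9, and where ANCOVA has 80% power the loss is about 12, 7 and 2 percentage points. Every correlation is assumed. If the correlation for body weight is high, as is likely, the gain is smallest for the secondary outcome the article discusses most; it would be larger for more variable measures.

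The Fisher test on the abstinence rate and the target of 300 are untouched, and the unadjusted results would not be invalid. Severity is low to moderate: a cheap improvement worth making, not a flaw that threatens the trial's main conclusion.

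**What to change.** In *Items analyzed and analytical methods*, replace the choice between t test and Wilcoxon as the main comparison with one prespecified ANCOVA for each continuous secondary endpoint:

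- Outcome: the 9-month value. Terms: arm, the baseline value of that outcome, and the minimization factors (age, sex, daily cigarettes, FTND score, SDS score). For the SDS endpoint, baseline SDS enters once.
- Report the adjusted mean difference with its 95% CI, in line with the stated "Two-tailed alpha of 5% and two-sided 95% confidence level will be used".
- Name in advance the indices expected to be skewed, such as TG, and analyse them on the log scale. Do not leave strongly skewed indices to raw-scale ANCOVA.
- Keep the Wilcoxon rank-sum test as a sensitivity analysis, and state that the ANCOVA result leads.

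The cost is a change of wording and slightly more analysis work. No new data and no change to the sample size are needed.

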#### Early termination of this study

The trial will be discontinued in the event of any of the following situations: (1) if the trial cannot be safely conducted due to serious adverse events; (2) if it is not possible to enroll the planned sample size; or (3) if it is not feasible to continue the study.

## Discussion

Exercise has various effects, including reduction in the risk of osteoporosis due to improvements in cardiovascular, musculoskeletal, and pulmonary function, and increased muscle mass, and prevention of obesity due to fat reduction and increased muscle mass, prevention of dyslipidemia due to reduced serum TG and increased HDL-cho, prevention of diabetes mellitus due to alleviation of insulin resistance, and prevention of hypertension due to improved vascular endothelial function and reduced blood pressure [16, 17]. Exercise also relieves stress and is an effective treatment for depression as it alleviates anxiety [18]. The 2013 Physical Activity Guidelines to Promote Health were formulated in Japan in 2013 [19] and included exercise as an important component.

Weight gain is common after quitting smoking [20] and impairs glucose tolerance [21–23], and may lead to smoking resumption [24, 25]. In this study, simple and safe exercises that can be easily performed by individuals who have gained weight after quitting smoking will be performed in accordance with a cardiac rehabilitation program. Participants will record their weight and step count, which should increase their self-efficacy. This study combines smoking cessation therapy and exercise therapy. If the study shows that exercise instruction improves the continuous abstinence rate, widespread implementation of the intervention is anticipated to reduce the public smoking rate, help to promote health, reduce medical expenses, and greatly benefit the public.

### Trial status

This study protocol is the first version since 10 December 2015. Recruitment began on 30 March 2016, and the expected recruitment completion date is December 2019. Recruitment to this study is ongoing at the time of manuscript submission.

## Data Availability

Not applicable.

## Abbreviations

EDC: Electronic data capture
FTND: Fagerstrom test for nicotine dependence
HDL-cho: High-density lipoprotein cholesterol
SDS: Self-rating depression scale
T-cho: Total cholesterol
TG: Triglyceride
